We run a large-scale natural field experiment to understand the behavioural processes that guide decisions to vaccinate and test alternative strategies to communicate the concept of herd immunity. The experiment varies the text of postal letters send to individuals eligible for free influenza vaccines. The experiment is run in collaboration with the municipal health authorities. The municipalities that have confirmed their participation in the study are: Espoo, Maalahti, Korsnäs, Närpiö, Kaskinen ja Kristiinankaupunki.

We implement the randomized study in municipalities with varying historical vaccination uptake rates (historical and current vaccination coverage based on the Finnish vaccination register). Implementation in different municipalities with different current vaccination rates will give further information about the generalizability of the findings in different cultural and socio-economic environments and may enable us to test the average indirect effect of the treatments (Spillover effect, see section 4.5)

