We identify using the Population Register all individuals who are born in year 1953 or before and resided in the participating municipality on July 01, 2018. We will obtain the postal addresses of these individuals using the Population Register and randomly assign individuals to treatment conditions that differ in the wording of the information material. Note that we will send the same letter separately to both individuals residing in the same address to avoid the situation that same persons living in the same household receive letters with different wordings. Importantly, the extract from the Population Register will also include an individual identifier (social security number) that can be used to match the received type of letter (treatment) with the actual vaccination decision recorded in the Care Register for Health Care to objectively evaluate the impact of received information on vaccination coverage. The matching of postal addresses and vaccination data will be conducted using pseudonymized identifiers. The pseudonymization of individual identifiers will be performed separately for both datasets by professional data management and data security staff of the National Institute for Health and Welfare. Consequently, the researchers conducting the data analysis will be able to access only pseudonymous data without a possibility to directly identify individuals from the data set. The data will be stored according to the data protection legislation and regulations of the National Institute for Health and Welfare during the research project.

We randomly assign individuals to treatment conditions that differ in the wording of the letters (attached). The authority’s standard letter serves as the baseline condition (T1). This letter is extended by communicating the concept of *herd immunity* and appealing to *pro-social preferences* by highlighting the fact that vaccinations may effectively prevent infections among people who are not able to vaccinate themselves (especially babies) (T2). To summarize, our study includes a control treatment (T0, no letter) and two treatment arms with the following contents: T1 – Standard letter, T2 – Herd immunity letter.

*4. Analysis Plan*

*4.1 Unit of Analysis*

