Our primary outcome variable is individual level vaccination decision. In addition, we estimate average treatment effects by municipality and test whether different treatment arms have uniform effects across municipalities that differ in their baseline vaccination coverage.

*4.2 Average treatment effects*

We run the following linear probability model to estimate the average treatments effects:

$Y_{i}=\alpha+\beta_{1}Mailing+\beta_{2}Herd+\varepsilon_{i}$,

where $Y_{i}$ indicates whether individual *i* has received an influenza vaccine by the end of influenza season 2018 - 2019. Variable *Mailing* indicates whether individual *i* is in a mailing group or in the control group receiving no mailings. Variable *Herd* is a treatment dummies indicating whether individual *i* belongs to a treatment arm with herd immunity information. We cluster standard errors at the household level to account for correlation at the household level.

In addition to our primary interest on the overall effectiveness of different treatment arms, we investigate the effect of mailings by municipalities that vary in their baseline vaccination rates and estimate the following equation using linear probability model:

$Y_{i,t}=\alpha+\beta_{1}{Mailing}_{t}+\beta_{2}{Baseline}_{t-1}+\beta_{3}Mailing*{Baseline}_{t-1}+\varepsilon_{i,t}$,

where variable *Baseline* denotes the vaccination coverage by municipality in the previous year (2017). Thus, $\beta_{3}$ shows the differential average treatments effect of mailing by municipality.

We run all estimations primarily using linear probability models to improve comparability between estimations as estimating equations with interaction terms and computing correct interaction effects in non-linear models may require tedious computing (Ai and Norton, 2003.

*4.3 Statistical power*

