We present in the following some standard power estimates to assess the minimum detectable effect size. Figure 1 shows the minimum detectable (absolute) effect size between two treatments as a function of sample size with test power .80 and .90. Power calculations are based on treatment comparisons using linear probability model. Here we assume that alpha = 0.05 (two-sided). Figure 2 shows the minimum total sample size needed to detect a standardized effect size varying from 0.05 to 0.25 (assuming test power .80 and alpha 0.05). Note that the power calculations do not account for potential corrections for multiple hypotheses testing or clustering of standard errors to account for potential correlation of standard errors.

[figure not shown]

Figure 1. Minimum detectable effect size as a function of sample size and statistical power.

[figure not shown]

Figure 2. Minimum total sample size needed to detect a standardized effect size varying from 0.05 to 0.25 (assuming test power .80 and alpha 0.05).

*4.4 Attrition*

We do not expect significant attrition. The expected main sources of attrition are migration from the municipality and mortality. Migration from the target municipality to abroad during study period is expected to be less than 5 percent. We expect that attrition is not correlated with the treatment status.

*4.5 Spillover effects*

Our RCT is based on household-level randomization. The institutional context, the large coverage of target groups and relatively short study period (from the reception of letter until the end influenza season) are likely to substantially limit potential spillover effects between the treatment arms and control group. We design the implementation of various treatment arms such that two (or more) individuals over 65-years of age living in the same household will be assigned to same treatment arm. This practice eliminates potential spillover effects between individuals living in the same household.

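### The primary model in section 4.2 contains no baseline covariates, which gives up precision that the planned registers could supply

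*Protocol*

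**What the plan says.** Section 4.2 of the protocol opens with "We run the following linear probability model to estimate the average treatments effects". The equation that follows has an intercept, an indicator for being in any mailing group, an indicator for the herd-immunity arm, and an error term. The outcome is whether the person "has received an influenza vaccine by the end of influenza season 2018 - 2019". On inference it says "We cluster standard errors at the household level to account for correlation at the household level". No adjusted version is mentioned.

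Three other places bear on what could be adjusted for:

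- **Section 3, Population Register extract.** Eligibility is set by birth year (1953 or before) and by municipality of residence on 1 July 2018, so both are known for every participant. The extract also carries a personal identifier, used to link the letter received to the person's vaccination record in the Care Register for Health Care.
- **Section 3, choice of municipalities.** Six are named, and past uptake is said to vary between them. The source is given as "historical and current vaccination coverage based on the Finnish vaccination register".
- **Section 4.2, secondary model.** The 2017 vaccination coverage of the municipality enters as a main effect and in an interaction with Mailing. This is the only use of previous-year vaccination in the analysis.

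**The concern.** The plan treats past vaccination as informative but uses it in its coarsest form. With six named municipalities, the 2017 coverage variable takes at most six values, and it is absent from the primary model. A person's own vaccination in the previous season is a natural candidate for a strong predictor of vaccination in the next. Under randomisation, adding a pre-randomisation covariate to a linear probability model leaves the target risk difference unchanged and removes explained variance from its error.

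Precision matters most for the Herd coefficient. The herd letter is the standard letter with added text, so the two arms share much of their content and a small difference is plausible. Section 4.3 also states that its power calculations allow for neither clustering nor multiplicity. The precision achieved will therefore be no better than those curves suggest if outcomes within households are positively correlated.

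**Working it through.** **The plan's own figures.** The text of section 4.3 states no sample size, target effect or minimum detectable effect, and the two figures are not in the text available, so there is no stated result to reproduce. Their inputs are described: Figure 1 shows the minimum detectable effect "as a function of sample size with test power .80 and .90", and Figure 2 the "minimum total sample size needed to detect a standardized effect size varying from 0.05 to 0.25". Alpha is 0.05, two-sided. For reference, with two equal arms (assumed), 80% power and no clustering, the total at a standardized effect of 0.05 is 2 × 2 × (1.960 + 0.842)² / 0.05², which is 12,560 after rounding up per arm.

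**Adjusting for own previous-season vaccination.** For one binary covariate, R² = φ², where φ is the correlation between vaccination in 2017–18 and in 2018–19. Residual variance is multiplied by 1 − φ², the standard error and minimum detectable effect by √(1 − φ²), and the sample size needed by 1 − φ². The value of φ is an assumption. If half were vaccinated in each season, φ equals the difference in current uptake between those vaccinated and not vaccinated last season. So 0.5 means 75% v 25%, and 0.7 means 85% v 15%.

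The last column assumes 5,000 per arm and 50% uptake. Unadjusted, the minimum detectable effect is then 2.802 × √(2 × 0.25 / 5,000) = 2.80 percentage points at 80% power.

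| Assumed φ | SE factor | N factor | Total N at effect 0.05 (unadjusted 12,560) | Power (unadjusted 80%) | Minimum detectable effect, points (unadjusted 2.80) |
|---|---|---|---|---|---|
| 0.3 | 0.954 | 0.91 | 11,430 | 84% | 2.67 |
| 0.5 | 0.866 | 0.75 | 9,420 | 90% | 2.43 |
| 0.6 | 0.800 | 0.64 | 8,039 | 94% | 2.24 |
| 0.7 | 0.714 | 0.51 | 6,406 | 97.5% | 2.00 |

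Household clustering inflates the absolute standard errors. The ratios hold approximately if the within-household correlation of residuals is similar after adjustment.

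**Adjusting for municipality only.** Suppose one municipality holds a share s of the sample, its coverage differs from the rest by g, and overall coverage is near 50%. Then R² = s(1 − s)g² / 0.25. All values here are assumed:

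- s = 0.8, g = 0.10: R² = 0.0064, SE factor 0.997.
- s = 0.7, g = 0.20: R² = 0.0336, SE factor 0.983.
- s = 0.8, g = 0.30: R² = 0.0576, SE factor 0.971.

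The gain is about 0.3–3%.

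**What municipality terms would protect against.** If the arms had different municipality mixes, the two-term model would carry bias equal to the difference in share times the coverage gap. For example, 0.10 × 0.20 = 0.02, or 2 percentage points. The protocol states no allocation ratio, overall or by municipality, so this is a conditional illustration only.

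**The case against.** The strongest reply is that nothing here is wrong. With randomisation and equal allocation shares, the two-term model with household-clustered errors is unbiased, gives valid inference and is easy to read. That stands. It could be added that covariates are usually left to a statistical analysis plan. That carries less weight, because the protocol writes out the primary equation in full.

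Three stronger readings are tempting, and the protocol does not support them:

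- **That each person's previous-season vaccination is already in the planned data.** Section 3 describes historical data only as coverage, from the Finnish vaccination register, and names the Care Register for Health Care for the individual outcome. Nowhere does it say that person-level 2017–18 records will be extracted.
- **That the gain is large and free.** No correlation is given, and at 0.3 the gain is about 5%. The 5,000 per arm and 50% uptake are illustrative and not in the protocol. With no stated sample size, the trial cannot be shown to be short of precision.
- **That the unadjusted estimate is confounded by municipality.** This needs unequal allocation shares, and silence on the split is not evidence of them. If shares did differ and effects varied by municipality, additive indicators would estimate a variance-weighted average effect and not the population average.

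The covariate also has a weak spot. People born in 1953 turned 65 only in 2018, and section 1 describes the recommendation and free offer as starting at 65. Their 2017–18 status may predict less well.

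**Conclusion.** The point holds as lost efficiency, not as an error. The protocol fixes a primary model without covariates while it holds municipality and birth year for everyone and has person-level linkage in hand. Most of the possible gain comes from own previous-season vaccination: standard errors lower by about 5% to 29% for an assumed correlation of 0.3 to 0.7. At 0.5, the gain equals a third more participants (1 / 0.75 = 1.33). That gain depends on person-level 2017–18 data being obtainable, which the protocol leaves open. Municipality indicators add little precision; their main use is as insurance against bias should allocation shares differ between municipalities. The omission itself is certain from the text. The size of the loss is not. The change is worth making before outcomes are seen, which also rules out a later choice of covariates.

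**What to change.** In section 4.2, prespecify as primary the linear probability model of vaccination on Mailing, Herd, municipality indicators, age (from birth year) and sex if it is in the extract, with household-clustered standard errors. Add own influenza vaccination in 2017–18 if person-level data for that season can be linked, and settle that before any outcome data are seen. Keep the present two-term model as a named sensitivity analysis.

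In section 3, reconcile the two register names: say which register supplies the individual outcome and whether it holds person-level records for the previous season. State the allocation ratio and whether it is the same in every municipality. If it is not, say which average effect the adjusted model is meant to estimate.

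The cost is one more linked variable, possibly a wider data permit (an assumption), and a slightly longer model. If 2017–18 records cannot be linked, the remaining adjustment is still simple, but little gain should be expected from municipality.
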